### Accrual/study duration considerations

We estimate accrual of 2–4 patients per month. As such, the study is projected to take between 1 and 2 years to accrue, with an additional 3 months required for follow-up. Patients who are eligible will be recruited in usual care settings by physicians. No additional promotional material will be made to recruit patients.

### Planned safety interim analysis

One interim analysis will be done once half of the patients (*n* = 24) have been accrued and their data are fully collected. The trial will be stopped if the rate of “inappropriate radiation” is ≥ 20% (*n* ≥ 5). Additionally, in the subset of patients where there is only 1 feasible site of biopsy and that site was irradiated, if the yield of histological diagnosis is < 80% or yield of molecular testing is < 70%, then no further patients will be enrolled where the site of radiation is the site of biopsy.

### Data analysis

Patients who decline a biopsy after RT will be excluded from analysis of both primary and secondary endpoints. Patients for whom biopsy is repeatedly non-diagnostic after undergoing RT will be masked from analysis of the primary endpoint, since inappropriate use of RT cannot be determined without a biopsy. However, analysis of secondary endpoints will be conducted, including determination of overall rates of diagnostic yields/accuracy, complications from biopsy, and number of biopsy attempts.

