## Background

In palliative radiation oncology, there is often a dilemma between the urgency of starting radiation treatment versus waiting for a biopsy for definitive diagnosis. Clinicians typically prefer waiting for a biopsy to confirm a malignancy prior to radiation, due to perceived risks of incorrect management (i.e. radiating a lymphoma or non-malignant lesion) and the possibility of radiation resulting in a non-diagnostic biopsy.

With increasingly stressed healthcare systems globally, biopsy wait times have lengthened, with the consequence of significantly delaying palliative radiation, sometimes by over a month in Canada. This comes at a high cost for patients, as their disease and symptoms continue to progress during the waiting period. Wait times for treatments have been associated with patient and caregiver anxiety, depression and poor quality of life [1].

Modern decision-making for patients in a palliative context requires a more nuanced balance of competing priorities for the patient, while taking into account the new realities in a publicly-funded healthcare system. Since dose/fractionation schemes for palliative radiation usually do not depend on the specific tumour histology, in some cases, physicians will elect to deliver radiation prior to biopsy, as part of shared decision making with the patient. However, to our knowledge, this approach has not been prospectively studied. RT-NOW is a single arm pragmatic trial with the goal of prospectively assessing this approach of delivering radiation before biopsy when warranted by symptom urgency, in carefully selected patients.

There are 4 main issues that clinicians are hoping to avoid when treating without a pathologic diagnosis:

Creating a non-diagnostic biopsy through radiation effects on tissue.Increasing the risk of biopsy complications.Treating a non-cancerous process.Treating a cancer that would be best managed with chemotherapy/systemic therapy as the primary treatment (i.e. lymphoma, small cell lung cancer, germ cell tumor).

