#### Secondary endpoint

Histological diagnostic accuracy, defined as the percentage of biopsies that yielded a histological diagnosis. This will include a comparison of diagnostic yield between biopsies done at radiated vs. non-radiated sites.Molecular testing accuracy, defined as the percentage of biopsies that yielded enough viable tissue for successful Next-Generation Sequencing testing using the ThermoFisher Oncomine V3 panel.Number of biopsy attempts required.Biopsy complication rates.Time from enrollment to first fraction of radiation.Time from enrollment to biopsy.Evidence of radiation effect in biopsy, defined as evidence of necrosis or dense fibrosis causing non-diagnosis in a lesion that had been radiated before the biopsy. If a biopsy was non-diagnostic because it was non-lesional, it would not be considered non-diagnostic as a result of radiation.Overall survival, defined as the time from enrollment to death from any cause or date of last follow-up, whichever occurs first.Edmonton Symptom Assessment Scale (ESAS) quality of life scores before RT and at first follow up (i.e. 4 weeks after RT).

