### Follow-up

In keeping with a pragmatic trial design [6], we will limit the number of additional follow-up visits beyond routine practice. We will do one follow-up either in person or over the telephone 4 weeks after RT or 2 weeks after biopsy, whichever is later. The purpose of this follow-up will be to assess for symptomatic response to radiation and monitor for adverse events from the biopsy. We will also obtain an ESAS score at the follow-up visit.

Post-treatment management questionnaires should be completed by the treating radiation oncologist (within 3 months of enrolment), which includes:

Biopsy result, including histological and molecular diagnosis.Biopsy complications.Preferred management plan if biopsy results were known prior to enrolment/radiation.

In addition, we will review the participant’s chart 1 year after enrolment, to determine the survivorship status of the patient.

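### Biopsy decliners are dropped from survival, time to first fraction and ESAS, which need no biopsy, and two sections disagree on when the follow-up ESAS is taken

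*Protocol article*

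**What the plan says.** **Exclusion rule.** The Data analysis section states: "Patients who decline a biopsy after RT will be excluded from analysis of both primary and secondary endpoints". Patients whose biopsies are repeatedly non-diagnostic are treated differently. They leave the primary analysis, because inappropriate radiation cannot be judged without a result, but they stay in the secondary analyses.

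**Endpoints that need no biopsy.** The Secondary endpoint section includes:
- "Time from enrollment to first fraction of radiation";
- overall survival, "defined as the time from enrollment to death from any cause or date of last follow-up, whichever occurs first";
- ESAS, as "quality of life scores before RT and at first follow up (i.e. 4 weeks after RT".

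Survival comes from a chart review 1 year after enrolment, "to determine the survivorship status of the patient" (Follow-up).

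**Timing of ESAS.** The Follow-up section schedules one visit, at "4 weeks after RT or 2 weeks after biopsy, whichever is later", and adds: "We will also obtain an ESAS score at the follow-up visit".

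**The concern.** There are two separate defects, and both lie in text that the article states.

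First, the exclusion covers more than its reason supports. A missing biopsy prevents judgement of inappropriate radiation, diagnostic yield or biopsy complications. It does not prevent anyone from knowing when radiation started, whether the patient is alive, or what the ESAS score was. Declining a biopsy happens after enrolment and treatment and may be related to how the patient is doing. Survival and symptom results restricted to patients who accepted a biopsy may therefore not describe the patients who were enrolled and irradiated.

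Second, the follow-up ESAS has two definitions. Under the visit rule, a patient with a late biopsy is scored later than the endpoint list says. The reported four-week result would then mix scores taken at different times after radiation. Patients who die or deteriorate before a later visit may give no score at all.

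**Working it through.** **1. Which endpoints need a biopsy.** The article lists nine secondary endpoints.
- Six need a biopsy: histological yield, molecular yield, number of attempts, complications, time to biopsy, and radiation effect in the specimen.
- Three do not: time to first fraction, overall survival and ESAS.

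Time to first fraction is complete before anyone can decline a biopsy after RT. Survival needs only the enrolment date and the one-year chart review. ESAS needs a baseline score and a follow-up contact.

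**2. Consistency within the article.** Non-diagnostic cases leave only the primary analysis, so the plan already separates endpoints that need a result from those that do not. It does not apply that separation to decliners. The section on discontinuation and withdrawal also asks for the end-of-study evaluation from removed subjects who consent. That fits poorly with discarding all of a decliner's secondary data.

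**3. The plan's own sample size.** Inputs from the statistics section: null rate 20%, expected rate 5%, one-sided 5% level, 90% power, 10% drop-out. The smallest exact binomial design is n = 44, rejecting the null with at most 4 events:
- P(X ≤ 4 | 0.20) = 0.0440
- P(X ≤ 4 | 0.05) = 0.9325

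Allowing for drop-out gives 44/0.9 = 48.9, or 44 × 1.1 = 48.4. The stated 48 is reproduced to within one patient. Nothing in this point changes it.

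**4. How large the survival distortion could be (hypothetical).** With N enrolled, d decliners, survival S_a at a fixed time in the others and S_d in decliners:

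overstatement = S_a − [(N − d)S_a + d·S_d]/N = (d/N)(S_a − S_d)

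Take N = 48. The values of d, S_a and S_d are assumptions that are not in the article. With S_a = 60%:

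| d | S_d = 60% | S_d = 30% | S_d = 10% |
|---|---|---|---|
| 2 | 0 | 1.25 points | 2.08 points |
| 5 | 0 | 3.13 points | 5.21 points |
| 10 | 0 | 6.25 points | 10.42 points |

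The sign reverses if decliners do better. With d = 5 and S_d = 90%, the result is (5/48)(60 − 90) = −3.13 points. The value d = 5 is 10% of 48 (4.8, rounded), which treats every drop-out as a decliner.

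For scale, the 95% half-width with 43 patients at 60% is 1.96 × √(0.6 × 0.4/43) = 14.6 points.

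**5. When the ESAS is taken.** For a biopsy w weeks after RT, the visit falls at max(4, w + 2) weeks:

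| Biopsy, weeks after RT | Visit, weeks after RT |
|---|---|
| up to 2 (or before or during RT) | 4 |
| 3 | 5 |
| 4 | 6 |
| 5 | 7 |
| 6 | 8 |

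The two definitions agree only when the biopsy falls no later than 2 weeks after RT. A decliner has no biopsy date, so the rule leaves the visit at 4 weeks. The exclusion then discards a score taken at the stated time.

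**The case against.** The strongest reply is that these are descriptive secondary endpoints of a single-arm trial whose aim concerns inappropriate radiation, biopsy complications and non-diagnostic biopsies. Specific points follow.

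- **Bias is not shown.** A reader might infer that the endpoints are biased, with survival too high. The article does not support that. Decliners might be deteriorating or might have had good symptom relief, and these act in opposite directions. For time to first fraction there is no evident mechanism beyond the lost data. This objection stands.
- **The 10% is not a count of decliners.** The sample-size section says only drop-out, which could include deaths, withdrawals or non-diagnostic biopsies. This stands, so five decliners is an illustration. Even then, the distortion is small beside the sampling error.
- **Benefit cannot be shown in any case.** It is tempting to say that these endpoints reveal whether patients gain from earlier radiation. Without a comparator they cannot, whichever patients are analysed. This stands.
- **ESAS drift affects only some patients.** The biopsy is to be done at the earliest possible time and may precede or overlap radiation. The Background's wait of "sometimes by over a month in Canada" describes how long biopsy can delay radiation, not the interval from radiation to biopsy. It makes late biopsies plausible but does not measure them. This stands.
- **One visit is deliberate.** It spares patients with limited life expectancy. Moving complications to chart review alone would weaken the active evaluation promised under Adverse events, and the Background itself warns that chart review may miss low-grade events. This stands and limits the choice of remedy.

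None of this supplies a reason to remove decliners from endpoints for which they have data, and none removes the mismatch between the two ESAS definitions.

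**Conclusion.** Both defects hold as matters of text. The exclusion reaches three endpoints that need no biopsy. It conditions them on a post-treatment choice and discards available data. The consequence is a risk of selection bias, mainly for survival and ESAS, of unknown size and direction. The survival figures above rest wholly on assumed decliner numbers and prognosis and should not be quoted as an estimate. The ESAS definitions conflict for patients biopsied more than 2 weeks after RT. How many that will be cannot be derived. It would be too strong to say that ESAS is generally not measured at four weeks. The primary endpoint and N = 48 are unaffected. The changes are worth making because they are cheap, not because the trial's main conclusion is at risk.

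**What to change.** **Exclusion.** Reword the Data analysis section so that decliners are excluded only from the primary endpoint and the biopsy-dependent secondary endpoints. Analyse overall survival and time to first fraction in all enrolled patients, and ESAS in all with a baseline score, reporting how many have a follow-up score. This costs a change of wording and needs no new data item.

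**ESAS timing.** Reconcile the Secondary endpoint and Follow-up sections in one of two ways:
1. Take ESAS at 4 weeks after RT for everyone, by telephone (already allowed), and keep the active biopsy-complication assessment at the later date. This costs one extra short contact for patients with a late biopsy, which departs somewhat from the single-visit design.
2. Redefine the endpoint as ESAS at the actual follow-up visit, and report the time since RT for each score. This adds no contact, but the scores will relate to different times after radiation.

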**Fig. 1 Fig1:**
[figure not shown]
General study schema

We hypothesize that with a radiation-before-biopsy approach, the rate of “inappropriate radiation” will be 5% or less. We hypothesize that the biopsy yields to establish a histologic and molecular diagnosis will be acceptable and comparable to our institutional averages of 90–95% and 80–90%, respectively. We hypothesize that the rates of complications will be acceptable and comparable to our institutional average of 5–10%.

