#### Biopsy

Biopsies should be taken at whichever site is clinically preferred, typically the most anatomically feasible site of biopsy (regardless of whether it has been irradiated), considering institutional wait times and availability for different biopsy procedures. If the first biopsy attempt is unsuccessful, the second attempt can be a repeat biopsy at the same site or at another site.

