#### Timing of biopsy and radiation

If the patient’s biopsy has not yet been ordered at the time of enrolment, it should be ordered immediately. The biopsy should be done at the earliest possible time, and if it is performed before radiation, or during radiation, the biopsy should proceed and the radiation should continue as planned. A biopsy may be completed before the patient is enrolled on trial as long as the biopsy result is not yet available at the time of enrolment (and at the start of radiation treatment).

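### Patients who decline a biopsy after radiation are removed from every secondary endpoint, although the reason given supports removal from the primary endpoint only

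*Protocol article*

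**What the plan says.** The Data analysis section of the protocol article treats two groups differently.

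- Decliners: "Patients who decline a biopsy after RT will be excluded from analysis of both primary and secondary endpoints".
- Repeated failures: "Patients for whom biopsy is repeatedly non-diagnostic after undergoing RT will be masked from analysis of the primary endpoint". The reason follows in the same sentence: without a biopsy, inappropriate use of radiation cannot be determined. These patients stay in the secondary analyses, "including determination of overall rates of diagnostic yields/accuracy, complications from biopsy, and number of biopsy attempts".

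Other sections bear on the rule:

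- Secondary endpoint: histological accuracy is "defined as the percentage of biopsies that yielded a histological diagnosis", so its denominator is biopsies. Molecular accuracy is also per biopsy. The list further contains overall survival, ESAS before and after radiation, and time from enrolment to first fraction.
- Biopsy: "If the first biopsy attempt is unsuccessful, the second attempt can be a repeat biopsy at the same site or at another site".
- Study design, hypotheses: histological and molecular yields should be "comparable to our institutional averages of 90–95% and 80–90%, respectively", and complication rates "comparable to our institutional average of 5–10"%.
- Planned safety interim analysis: among patients whose only feasible biopsy site was irradiated, a histological yield below 80% or a molecular yield below 70% ends further enrolment of patients irradiated at the biopsy site.

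**The concern.** Declining a biopsy happens after treatment. The trial asks what follows when radiation comes before the biopsy result, and a patient who is irradiated and then declines is one of the outcomes of that approach. The stated reason for exclusion concerns only whether radiation was appropriate. It gives no ground for discarding the patient's survival, symptom scores or time to radiation.

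The Discussion names, among the main risks, the effect of a non-diagnostic biopsy on systemic therapy options. A patient with no tissue at all is in a similar position, yet is counted in no endpoint.

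There is also a gap between the two groups. Only patients whose biopsies fail *repeatedly* are expressly kept. A patient with one failed biopsy after radiation who refuses the foreseen repeat is not in that group, and could be read as having declined a biopsy after radiation. A failed first attempt is a plausible reason for refusing a second, so under that reading the exclusion would depend on the outcome being measured. The interim rule is where this could change a decision.

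**Working it through.** **Plan's own figure.** Inputs from Statistics and sample size calculations: null rate 20%, expected rate 5%, one-sided 5% level, 90% power, 10% drop-out, N = 48. The smallest exact binomial design meeting both limits has n = 44, rejecting at 4 or fewer events (level 0.0440, power 0.9325). With drop-out, 44 × 1.1 = 48.4, or 44/0.9 = 48.9. The stated 48 is reproduced to within a patient. Nothing below changes it.

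**Step 1: which secondary endpoints need a biopsy?**

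| Endpoint | Needs a biopsy? | Effect of excluding a never-biopsied patient |
|---|---|---|
| Histological and molecular yield | Yes, per biopsy | None: no biopsy to count |
| Biopsy complications, radiation effect in biopsy | Yes | None: nothing to count |
| Overall survival | No | Patient lost |
| ESAS before and after radiation | No | Patient lost |
| Time to first fraction | No | Patient lost |

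The exclusion therefore does harm where no biopsy is needed. For yield, the per-biopsy definition already leaves out the never-biopsied.

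**Step 2: what the per-biopsy yield does not show.** The article gives no decliner rate. Assume 5 of 48 decline (about 10%), leaving 43 patients with one biopsy each.

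- 41 diagnosed: 41/43 = 95.3% per biopsy; 41/48 = 85.4% of irradiated patients.
- 39 diagnosed: 39/43 = 90.7% per biopsy; 39/48 = 81.3% of irradiated patients.
- Range with per-biopsy yield near 95%: 1 decliner gives 45/47 = 95.7% and 45/48 = 93.8%; 10 decliners give 36/38 = 94.7% and 36/48 = 75.0%.

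**Step 3: if refusing a repeat counts as declining.** Assume 43 patients with one biopsy each, 3 non-diagnostic, and 2 of those 3 refusing a repeat.

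- All biopsies kept: 40/43 = 93.0%.
- The two refusers removed: 40/41 = 97.6%.

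For complications, a patient is lost only if the biopsy failed, a complication occurred and the repeat was refused. Using the article's benchmarks and assuming independence, the expected number with both failure and complication is 43 × 0.05 × 0.05 = 0.1 to 43 × 0.10 × 0.10 = 0.4 (histological failure), and at most 43 × 0.20 × 0.10 = 0.9 (molecular failure), before any refusal. Losing one such patient moves 4/43 = 9.3% to 3/42 = 7.1%. A larger shift is possible but unlikely.

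**Step 4: the interim rule.** Assume 8 single-site patients with one biopsy each, 6 diagnosed, and 2 who fail once and refuse a repeat. Assume also that the exclusion applies at the interim.

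- All biopsies kept: 6/8 = 75%, below 80%, so the rule fires.
- Refusers removed: 6/6 = 100%, so it does not.

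This depends on subset size, which the article does not give. With 10 patients and the same two failures, 8/10 = 80% is not below 80%, and the rule would not fire either way.

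**The case against.** The strongest reply is that declining a biopsy after radiation most naturally means having none. Someone biopsied once has not declined, and the section's evident intent is to count failures, since repeated failures are kept. This stands in part: the loss of failed first biopsies is one permitted reading, not what the text states. The article does not settle the case, however, and it could otherwise be settled after results are known.

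A second reply is that patients without a biopsy cannot distort a per-biopsy yield or complication rate. This stands fully. A reader might infer that excluding decliners in itself raises yield and lowers complications; under the article's definitions it does not. Nor may the 85% in Step 2 be set against the 90–95% benchmark, which refers to biopsies.

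Third, the sizes are assumed. Drop-out is not defined and may already include repeated failures, in which case 43 evaluable patients would mean 43/48 = 90% diagnosed. This stands, and the figures are offered only as illustrations.

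Fourth, declining cannot be blamed on the sequence. There is no comparator, patients waiting for a biopsy may also decline one, and the biopsy need not follow radiation: "if it is performed before radiation, or during radiation, the biopsy should proceed and the radiation should continue as planned". This also stands, and no causal claim is made here.

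Finally, patient flow and extra denominators are often left to a fuller document. That is fair for reporting detail, but the exclusion is a rule the article states, and its scope exceeds its reason.

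**Conclusion.** The point holds in limited form. The exclusion is too wide: it removes patients, because of a post-treatment event, from three endpoints that need no biopsy, for a reason that reaches only the primary endpoint. Together with the per-biopsy yield, it leaves no endpoint showing how many irradiated patients lack a diagnosis. If 5 of 48 declined, the gap would be 95% against 85%; for 1 to 10 decliners the patient-level figure runs from 94% to 75%. All of this rests on an assumed number of decliners and one biopsy per patient.

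The placement of a patient with one failed biopsy and a refused repeat is an ambiguity, not a stated deletion. If such patients are excluded, yield rises, complications may fall slightly, and the interim yield rule could fail to fire in a small subset. The documents do not support saying that failed or complicated biopsies will disappear from the results, or that the reported yield is biased in general. The primary test and N = 48 are untouched. The change should be made, but it concerns secondary endpoints and one interim safety rule.

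**What to change.** In the Data analysis section:

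1. Limit the exclusion of decliners to the primary endpoint, and keep them in the secondary endpoints that need no biopsy (overall survival, ESAS, time to radiation).
2. State that every biopsy actually performed stays in the yield, complication and attempts analyses, and in the interim yield rule, whether or not a repeat is refused.
3. Next to the per-biopsy yield, report the proportion of all irradiated patients with a histological diagnosis, with the reasons for having none. Present it as a separate quantity, not against the institutional per-biopsy averages.

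The cost is a few sentences and one extra results row. The data come from the follow-up visit, the post-treatment questionnaire and the one-year chart review already planned. The downside is that the diagnostic figure may look less favourable.
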